### Sample size

The primary outcome in this trial is the change of the Visual Analogue Score (VAS) of average pain in the menstrual period between the baseline (Visit 2) and after treatment (Visit 4). The hypothesis is

H0:δ=Δ1-Δ2=0

H1:δ=Δ1-Δ2≠0

Δ1: The change of VAS score between Visit 4 and baseline in GJBNH group

Δ2: The change of VAS score between Visit 4 and baseline in placebo control

As a reference, we have chosen the study of Choi et. al. [6] and Yeh LL [9]. The mean (± standard deviation, SD) change of the VAS in GJBNH group (n = 13) was 2.42 (± 2.04) and those in placebo control group (n = 38) was 1.08 (± 2.14). We used the mean difference between groups, 1.34 (= 2.42-1.08), as a clinically significant improvement worth to detect and 2.12 as its pooled standard deviation. With 5% of two-sided significance level and 80% of statistical power, we needed to randomly assign fifty participants in each group considering approximately 20% of drop-out rate.

### Randomization

Participants will be given a random number at Visit 2. When a participant makes the second visit to the trial site, the investigator will connect to the Medical Research Collaboration Center (MRCC) web site run by Seoul National University Hospital which is commissioned for the allocation process in this trial. To randomize, the investigator will connect to the MRCC website (http://mrcc.snuh.org) and input patient's number and birthday, and confirm that the patient fulfil the inclusion and the exclusion criteria. Then, a random number is generated. No one except the researcher at the MRCC can know whether the number indicates treatment group or placebo group, and all participants, investigators, and monitors are blinded.

### Statistical method

Efficacy analysis will be performed for both ITT (intention-to treat, all randomly assigned participants) and PP (per-protocol, participants completed the trial without any protocol deviations) data sets. To compare the differences of the average changes of the VAS between the experimental arm and the control arm, the Short Form McGill Pain Questionnaire score, the blood stagnation score, the Cox menstrual score from the baseline (Visit 2) to after the treatment (Visit 4) between two groups, and analysis of covariance (ANCOVA) using the baseline score as a covariate will be used.

For the variables which measure the autonomic nerve system (HF, high frequency; LF, low frequency; HF/LF ratio), similar methods described above or their corresponding non-parametric analysis will be performed as appropriate.

For ITT analysis, missing data will be imputed by MI (Multiple Imputation) method using SAS/MI procedure.

The safety data set will include the participants who take the intervention at least once. For safety analysis, physical examination and self-reported adverse event will be compared by the chi-square test. In addition, the results of liver function tests, blood cell count and urine analysis will be analyzed using the same methods as described in efficacy analysis after classifying these results into normal or abnormal according to their respective normal ranges. The chi-square test will be used to compare the differences between the groups.

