### Setting

This trial is a randomized, double-blind, parallel group, placebo-controlled phase IV trial. There are three investigational sites: Oriental Medicine Obstetrics and Gynecology Clinic of Kyung Hee Medical Center in Seoul, Obstetrics and Gynecology Clinic of Won Kwang Oriental Hospital in Gunpo, and Obstetrics and Gynecology Clinic of Kyung Won Gil Oriental Medical Hospital of Kyung Won University in Incheon, Korea. Participants will be treated as outpatients in these sites. Before the beginning of the trial, the protocol of the trial has been approved by the Institutional Review Board (IRB). All participants will take GJBNH or placebo for two menstrual cycles (about eight weeks). They will be followed up during three menstrual cycles. It takes five menstrual cycles (about 20 weeks) from baseline to finish. The total span from screening (visit 1) to finish (2^nd ^follow-up) can vary according to the participant's period. Figure 1 is an overview of this trial.

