### Rescue medication

Ten pain killer pills will be given during each treatment cycle as rescue medication. If the participant can not endure the pain, she can take the rescue medication. But all participants should not take any pain-killer except given by the investigator. If the participant takes any other drug than what is given from the trial, it should be described in the case-report form (CRF). Any participant taking drugs that can influence the outcome such as NSAIDs or oral contraceptive pills will be excluded from the trial.

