### Outcomes

#### Primary outcome

The primary outcome in this study is the change in the Visual Analogue Scale (VAS) of average menstrual pain between the baseline (Visit 2) and after the treatment (Visit 4). A 100 mm VAS will be used to assess average level of pain during the menstrual period.

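### The per-protocol set for the Visit 4 endpoint is defined over the whole trial and by any deviation, so it drops women with valid Visit 4 data because of later or trivial events

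*Protocol article*

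**What the plan says.** The protocol article fixes four things that bear on this point.

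- **Analysis sets (Statistical method).** "Efficacy analysis will be performed for both ITT (intention-to treat, all randomly assigned participants) and PP". The second set is described as "PP (per-protocol, participants completed the trial without any protocol deviations) data sets". The same section applies ANCOVA to the changes from Visit 2 to Visit 4 and gives multiple imputation for missing data in the ITT analysis.
- **Primary endpoint (Primary outcome; repeated under Sample size).** The change in VAS of "average menstrual pain between the baseline (Visit 2) and after the treatment (Visit 4").
- **Length of the trial (Setting).** Study treatment lasts two cycles, or roughly eight weeks. For the time after treatment the section says: "They will be followed up during three menstrual cycles". The overall duration is then given as follows: "It takes five menstrual cycles (about 20 weeks) from baseline to finish". The Abstract and the Setting section both identify the end as the second follow-up, which the Abstract numbers Visit 6.
- **Painkillers (Rescue medication).** Rescue pills are described for each treatment cycle. The text continues: "But all participants should not take any pain-killer except given by the investigator". No time span is attached to that restriction.

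**The concern.** The time window of the PP set does not match that of the endpoint it is used for. The endpoint closes after two cycles, while PP membership is decided over five cycles and lost through any deviation, however small. Nothing that happens in cycles 3 to 5 can change a VAS already recorded at Visit 4, yet it can remove that value from the analysis.

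Two things are at stake. The first is precision, because usable primary data are discarded. The second is bias: selecting on events after the endpoint distorts the comparison if those events are related to pain and occur at different rates in the two arms. Painkiller use in follow-up is a plausible example. If the restriction on other painkillers runs to the end of the trial, a woman who treats her own pain in cycles 3 to 5 has deviated, and women with more pain are more likely to do so. If GJBNH works and the benefit lasts, that would happen more often on placebo.

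**Working it through.** **1. The plan's own figure.** Inputs from Sample size: difference 1.34, SD 2.12, two-sided 5%, power 80%, about 20% drop-out.

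n per arm = 2 × (1.96 + 0.8416)² × (2.12/1.34)² = 39.3, rounded up to 40; 40/(1 − 0.20) = 50. The stated 50 per arm is reproduced. The 20% allowance names no time point, so it is not clear whether it covers losses to Visit 4 only or all exclusions over five cycles.

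**2. Time windows side by side.**

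| | Closes at |
|---|---|
| Treatment | end of cycle 2 |
| Primary endpoint | Visit 4 |
| PP membership | end of trial: Visit 6, five cycles from baseline |

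The gap is three cycles of follow-up.

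**3. Precision.** Standard error = 2.12 × √(2/n); power = Φ(1.34/SE − 1.96).

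| PP women per arm | SE | Power |
|---|---|---|
| 40 | 0.474 | 0.807 |
| 35 | 0.507 | 0.753 |
| 30 | 0.547 | 0.687 |
| 25 | 0.600 | 0.608 |

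For example, suppose 40 per arm reach Visit 4 without a problem and five of them leave PP for later events. The standard error then rises by about 7% (0.507/0.474). The counts below 40 are assumptions; the article gives no expected deviation rate.

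**4. Bias with a true effect (all inputs beyond 1.34 and 2.12 are assumed).** Visit 4 pain is normal with SD 2.12 and 1.34 lower on GJBNH. Follow-up pain has the same SD, the same 1.34 difference (the effect persists in full) and a within-arm correlation of 0.7 with Visit 4 pain. The log-odds of leaving PP rise by ln(OR) per point of follow-up pain, by the same rule in both arms. The intercept is set so that 10%, 20% or 30% of placebo women leave. The PP difference, simulated with 3 million per arm, is:

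| Placebo women excluded | OR 1.5 | OR 2 |
|---|---|---|
| 10% | 1.30 | 1.25 |
| 20% | 1.27 | 1.20 |
| 30% | 1.24 | 1.16 |

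The shift is 0.04 to 0.18, towards no difference, against a standard error of 0.474. If the effect does not persist into follow-up, the two arms lose equal shares and the difference stays at 1.34.

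**5. Bias with no true effect at Visit 4.** Suppose the women with the most follow-up pain are excluded, a share p in each arm, with correlation ρ. Mean Visit 4 pain among those kept falls by ρ × 2.12 × φ(z)/(1 − p), where z is the upper p point. The factor φ(z)/(1 − p) is 0.195 at 10%, 0.350 at 20% and 0.497 at 30%.

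- 10% against 20%: 2.12 × (0.350 − 0.195) = 0.33; times ρ of 0.3 to 0.7 gives 0.10 to 0.23.
- 10% against 30%: 2.12 × (0.497 − 0.195) = 0.64; times ρ of 0.3 to 0.7 gives 0.19 to 0.45.
- Equal shares: zero.

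The arm with more exclusions looks better than it is.

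**The case against.** **ITT is unaffected.** That set contains all randomised women, so no Visit 4 value is lost from the trial as a whole. A strict set of deviation-free completers shown beside ITT is a recognisable convention. This stands, and it is why the point is minor.

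**The bias is assumed and modest.** Exclusion rates, odds ratio and correlation are not in the document. In the case where the treatment works, the shift is well under one standard error and makes a PP claim harder, not easier. This stands too. The figures show what could happen, not what will.

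**The painkiller route is an inference.** The restriction comes directly after the supply for treatment cycles and has no stated time span. The article does not say that rescue is unavailable in follow-up, and it has pill counts recorded at every visit. A reader might infer that a follow-up painkiller is certainly a deviation. The literal wording allows this but does not state it. A missed follow-up visit is enough to make the point without it.

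**The SAP may settle it.** For the grading of deviations in general, that is fair. But the article states a PP rule, and an SAP that limited PP to major deviations up to Visit 4 would have to depart from that rule.

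**A tempting stronger reading.** A reader might infer that, because both sets are named with no order between them, success could be claimed on whichever is significant, and that the 5% level is therefore exceeded. With the two test statistics correlated at the square root of the PP share, an either-set rule would give 7.1% at a share of 80% and 8.3% at 50%. The document does not support this as an error. It nowhere says that either set may carry the claim, and the order of analysis sets is commonly left to the SAP or full protocol. The PP shares are assumed. The formula also ignores multiple imputation in ITT: a woman lost before Visit 4 adds little independent information, so the two analyses would be closer than it supposes.

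**Conclusion.** The point holds for the PP definition, at minor severity. As written, the PP analysis of a Visit 4 endpoint is restricted by events up to Visit 6 and by deviations of any size. The loss of valid Visit 4 data follows from the text, taking completion of the trial to mean reaching the second follow-up, as the Setting section does. How many women are lost cannot be known from the article.

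Bias is possible but conditional: later exclusions must depend on pain and differ by arm. Under the inputs assumed above, a true 1.34 is estimated as about 1.16 to 1.30, and with equal exclusion rates the bias is about zero. The ITT estimate, the sample size and the stated significance level are not called into question. Stating which set is primary would be a useful clarification, but its absence here is not a demonstrated type I error problem.

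**What to change.** Replace the PP definition for the Visit 4 analyses with wording such as: *The ITT analysis at Visit 4 is primary and the per-protocol analysis is supportive. For Visit 4 outcomes the per-protocol set consists of randomised participants with baseline and Visit 4 VAS and no major protocol deviation up to Visit 4. Deviations are listed and classified as major or minor before unblinding. Deviations after Visit 4 affect only the follow-up analyses.*

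The sponsor should also state whether the restriction on other painkillers reaches into the follow-up cycles, so that the deviation list can be drawn up without guesswork. What that rule should be is outside this point.

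The cost is a few sentences and a blinded deviation review. No new data, visits or participants are needed. The change has to be made before unblinding, because a set redefined afterwards would not be credible.

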**Methods:**

This study is a multi-centre, randomised, double-blind, controlled trial with two parallel arms: the group taking GJBNH and the group taking placebo. 100 patients (women from age 18 to 35) will be enrolled to the trial. Through randomization 50 patients will be in experiment arm, and the other 50 patients will be in control arm. At the second visit (baseline), all participants who were already screened that they fulfil both the inclusion and the exclusion criteria will be randomised into two groups. Each group will take the intervention three times per day during two menstrual cycles. After the treatment for two cycles, each patient will be followed up during their 3^rd^, 4^th ^and 5^th ^menstrual cycles. From the screening (Visit 1) through the second follow-up (Visit 6) the entire process will take 25 weeks.

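### The stated ANCOVA for this three-hospital trial names the baseline score as its only covariate; centre should be prespecified as a fixed factor (minor)

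*Protocol article*

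**What the plan says.** - **Design.** The abstract's Methods paragraph states: "This study is a multi-centre, randomised, double-blind, controlled trial with two parallel arms". The Setting section says "There are three investigational sites" and lists hospitals in Seoul, Gunpo and Incheon.
- **Analysis.** For the change in average-pain VAS from Visit 2 to Visit 4, and for the McGill, blood stagnation and Cox scores, the Statistical method section says "analysis of covariance (ANCOVA) using the baseline score as a covariate will be used". Centre is not mentioned there. The abstract's Discussion paragraph adds a repeated measures ANOVA, also without centre. Missing data in the ITT set are to be multiply imputed; the imputation variables are not listed.
- **Allocation.** Under Randomization, the investigator is to go to a central website, "input patient's number and birthday, and confirm that the patient fulfil the inclusion and the exclusion criteria". The next sentence reads: "Then, a random number is generated". Stratification and blocking are not mentioned in either direction.
- **Sample size.** Fifty per arm, from a difference of 1.34, with "2.12 as its pooled standard deviation", and "With 5% of two-sided significance level and 80% of statistical power", allowing for about 20% drop-out.

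**The concern.** Entry requires a diagnosis of blood stagnation by two specialists, and the primary outcome is a self-rated pain score. Both can plausibly differ between hospitals. Adjusting for baseline removes centre differences that already show in the baseline score. It does not remove centre differences in how patients respond or report at Visit 4; these go into the error term.

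The consequence depends on how allocation was done:

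- **Stratified by site.** The arms are balanced within centres, so centre does not add to the true variance of the treatment difference. A model without centre still counts it in the standard error, which is then too large, and the test rejects too rarely.
- **Not stratified.** The test keeps its size, but the treatment estimate carries avoidable noise from uneven splits within centres.

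The sample size leaves little reserve above 80% power, so modest precision is worth having if it is cheap.

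**Working it through.** **Inputs from the article (Sample size):** difference 1.34, SD 2.12, two-sided 5%, power 80%, drop-out about 20%. **Assumed, because the article gives no figure:** the share r of residual variance due to centre, taken as 0%, 5% and 10%, and three centres of similar size.

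**1. The plan's own figure.** n per arm = 2 × [2.12 × (1.960 + 0.842) / 1.34]² = 39.3, rounded up to 40. Then 40 / 0.8 = 50 per arm. This reproduces the stated number, and the point here does not change it. The t-test power at 40 completers per arm (78 df) is 79.7%.

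**2. Unstratified allocation, centre added.** Two effects oppose each other. The residual variance falls by the factor (1 - r). Treatment and centre are also not exactly orthogonal: with 80 completers and 2 df for centre, an expected 2/79 = 2.5% of the treatment information is lost. So

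effective n per arm = 40 × (1 - 2/79) / (1 - r), tested on 76 df.

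| r (assumed) | Effective n per arm | Power without centre | Power with centre | Change |
|---|---|---|---|---|
| 0% | 39.0 | 79.7% | 78.7% | -1 point |
| 5% | 41.0 | 79.7% | 80.7% | +1 point |
| 10% | 43.3 | 79.7% | 82.8% | +3 points |

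Break-even is where 1 - r = 1 - 2/79, that is r of about 2.5%. A simulation of 80 completers in three centres (40,000 runs per setting, baseline left out of both models) gave 79.8% without against 78.7% with centre at r = 0%, 79.7% against 80.7% at 5%, and 79.6% against 82.7% at 10%. Size without centre was 4.9%, 5.0% and 5.2%, which is nominal.

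**3. Stratified allocation, centre omitted.** The standard error is too large by the factor 1/√(1 - r), so

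actual size ≈ 2 × [1 - Φ(1.96 / √(1 - r))].

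- r = 5%: 1.96 / √0.95 = 2.011, size 4.4%.
- r = 10%: 1.96 / √0.90 = 2.066, size 3.9%.

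Simulation of the same design, stratified, gave 4.3% and 3.9%. Allowing for simulation error and different centre sizes, 4.3-4.5% and 3.6-4.1% are fair ranges. With centre in the model the simulated size was 4.8% and 5.0%. Here treatment and centre are orthogonal, so at r = 0% adding centre costs almost nothing (79.7% either way).

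**4. Limit of the calculation.** It uses the change-score SD of 2.12. The planned ANCOVA has a residual after baseline adjustment, which the article does not give. The share r should therefore be read as what centre still explains after baseline, and the power figures as indications.

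**The case against.** **The article names baseline but does not say that nothing else enters the model.** This is correct; that no other covariate is named is an observation about the text. A centre term could stand in the full protocol or the SAP, neither of which is shown. If so, the point closes by aligning the text. It is still fair to raise, because the article states a specific model with a specific covariate for a design it calls multi-centre.

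**A reader might infer from the randomisation step that allocation ignores site.** The article does not support that. It lists what the investigator enters, and the patient number or the site login may identify the hospital. Stratification and block size are also details that an article commonly leaves out. Chance imbalance between centres is possible but not shown, and the point does not rest on it.

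**A reader might also infer that a centre term helps in every case.** It does not. With unstratified allocation and no centre effect it costs about one point of power, and below a share of about 2.5% it is a small net loss.

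**Validity is not at risk.** This stands in full. The estimate is unbiased on average either way, type I error is nominal if allocation is unstratified, and the test errs on the conservative side if it is stratified.

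**Conclusion.** The point holds as a minor one. The stated model leaves centre in the residual in a three-hospital trial, and prespecifying centre is the better choice unless centre explains almost nothing after baseline. The size is modest: about -1 to +3 points of power under unstratified allocation, or a test running at roughly 3.6-4.5% instead of 5% under stratified allocation, for assumed centre shares of 0-10% and 5-10% respectively. The documents give no between-centre variance, so these are ranges and not estimates. Nothing here shows a false-positive risk, a biased estimate or a wrong sample size.

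**What to change.** Before unblinding:

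1. State the model as ANCOVA with treatment, baseline score and centre (fixed factor, 2 df) for the primary outcome and the continuous secondary outcomes.
2. Include centre in the multiple-imputation model, so that imputation and analysis agree.
3. State whether the web allocation is stratified by site. If it is, the centre term is needed for the test to run at its nominal level.

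The cost is a line or two of analysis text and two degrees of freedom. If centre explains nothing, about one point of power is lost under unstratified allocation and practically none under stratified allocation. The sample size need not change. Fixing the choice in advance also avoids a decision about centre adjustment after the results are known.

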### Safety assessment

All participants will report any adverse event she had while taking the intervention at every visit. Every adverse event will be described in the CRF. If the adverse event is severe and associates with the trial, the participant will be withdrawn from the trial and appropriate treatment will be given to her. For safety assessment, a liver function test, blood cell count test, physical examination, and urine analysis will be carried out at Visit 4.

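### Liver-function and blood-count results are compared only as normal/abnormal flags, which has much lower power for a whole-group shift than comparing the measured values

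*Protocol article*

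**What the plan says.** Under Safety assessment, the protocol article states that "a liver function test, blood cell count test, physical examination, and urine analysis will be carried out at Visit 4". Under Statistical method, "The safety data set will include the participants who take the intervention at least once". The laboratory results are to be analysed by the methods of the efficacy analysis, but "after classifying these results into normal or abnormal according to their respective normal ranges". The paragraph then closes: "The chi-square test will be used to compare the differences between the groups".

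So the order is fixed: classify first, then compare the classes. The reference to the efficacy methods does not restore an analysis of measured values, because the classification precedes it and chi-square is the test named. The same section analyses the pain, blood stagnation and menstrual symptom scores by ANCOVA on their own scale, and the heart-rate variables by similar or non-parametric methods. The article gives no reason for treating numeric safety results differently. It states no expected abnormal rate, laboratory distribution or power for the safety comparison.

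**The concern.** Liver function tests and blood counts give numbers. Reduced to one flag each, any movement inside the normal range disappears, and when abnormal values are uncommon only a few women per arm carry information. A blood count has a lower and an upper limit. If one abnormal category covers both, a shift that pushes some women above the upper limit while lifting others off the lower limit partly cancels.

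At stake is how a null laboratory result can be interpreted. With 50 or fewer women per arm, a non-significant chi-square on a handful of flags says little about whether the herbal formula moved the group as a whole, although the values that bear on that question will already have been collected.

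**Working it through.** **Inputs from the protocol article.** "Through randomization 50 patients will be in experiment arm, and the other 50 patients will be in control arm" (abstract, Methods). "With 5% of two-sided significance level and 80% of statistical power", and "considering approximately 20% of drop-out rate" (Sample size); both are stated for the primary outcome only.

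**The plan's own figure.** "We used the mean difference between groups, 1.34 (= 2.42-1.08), as a clinically significant improvement worth to detect and 2.12 as its pooled standard deviation". Then n = 2 × (1.960 + 0.842)² × (2.12/1.34)² = 39.3, so 40 per arm, and 40/0.80 = 50. The stated 50 per arm reproduces. Between 40 (completers) and 50 (all randomised) women per arm can therefore contribute a Visit 4 laboratory value.

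**Assumptions, because the article gives no laboratory figures.** Values are normal with SD 1 after a suitable transformation. Every treated woman shifts by d SD. Tests are two-sided at 5%. The share b of placebo women beyond one limit is 2.5%, 5% or 10%. A two-sided range with 5% of placebo women outside is also considered.

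**Formulas.**
- Measured scale: power of the two-sample t-test at standardised difference d.
- One-limit flag: the treated abnormal rate is 1 − Φ(z₁₋b − d). Power of the Pearson chi-square is obtained by exact enumeration of the two binomials.
- Two-sided flag: the treated abnormal rate is 1 − Φ(1.96 − d) + Φ(−1.96 − d).

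**Worked case, d = 0.5.** With b = 2.5%, the treated rate is 1 − Φ(1.46) = 7.2%. At 50 per arm that is 1.25 against 3.6 expected abnormal women. For the two-sided range, the upper tail rises from 2.5% to 7.2% while the lower tail falls from 2.5% to Φ(−2.46) = 0.7%. The flag therefore moves only from 5.0% to 7.9%.

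**Power in %, at 40 / 50 women per arm**

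| Shift | Measured scale | Flag, b = 2.5% | Flag, b = 5% | Flag, b = 10% | Flag, two-sided range |
|---|---|---|---|---|---|
| 0.3 SD | 26 / 32 | 5 / 7 | 11 / 11 | 14 / 16 | 5 / 5 |
| 0.5 SD | 60 / 70 | 15 / 17 | 25 / 26 | 31 / 38 | 9 / 8 |
| 1.0 SD | over 99 | 67 / 73 | 79 / 88 | 88 / 94 | 44 / 51 |

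**The same loss in numbers of women.** At 50 per arm, the measured scale has 80% power for a shift of 0.566 SD. For that shift the flag has 22%, 34% and 47% at b = 2.5%, 5% and 10%, and 10% for the two-sided range. To reach 80%, the flag would need about 246, 165 and 116 women per arm, and about 717 for the two-sided range.

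**The opposite pattern of harm.** Suppose 10% of treated women shift by 3 SD and the rest not at all. By simulation, with b = 2.5%, the flag has about 33-37% power and the comparison of means 19-23%. The flag's advantage shrinks to about nil at b = 10%.

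**The case against.** The strongest reply is that a normal/abnormal count is a defensible safety analysis. It looks for out-of-range values, and when harm falls on a few women it can beat the comparison of means, as shown above. A uniform shift favours the mean by construction, nothing in the article says which pattern is plausible for this formula, and no passage shows that a shift inside the normal range matters clinically. This stands. It is a reason to keep the flag, but not to make it the only comparison.

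Further, the article sets efficacy objectives only. It has no laboratory hypothesis and makes no power claim for safety. Numeric summaries, transformations and table layout are commonly left to an analysis plan, and the article does not exclude descriptive summaries of the values. This also stands, and it limits the weight of the point. It does not remove it, because the between-arm comparison itself is specified on the cut values.

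A reader might infer that the planned analysis is bound to miss a shift that the measured values are bound to find. The figures do not support that. At 1 SD the one-limit flag usually succeeds, and at 0.3 SD neither analysis is reliable. Nor should the standardised effect of the sample size calculation, 1.34/2.12 = 0.63 SD, serve as a benchmark here. It is a pain-score difference and has no bearing on liver enzymes or blood counts.

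**Conclusion.** The point holds as a loss of power for a shift of the whole group. Under the stated assumptions the loss runs from modest at 0.3 SD, where both analyses are weak, to large at 0.5 SD (15-38% against 60-70%). It narrows again at 1 SD for a single limit. The two-sided range fares worst, with about 8-9% at 0.5 SD. The direction is the same at every placebo abnormal rate examined, but the size depends on that rate, on normality after transformation and on a common shift, none of which the article supplies.

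Two stronger conclusions are not supported: that the flag is inferior for every form of harm, and that the trial's conclusions are at risk. Safety is secondary and unpowered, and the primary comparison is untouched. This is a worthwhile and cheap improvement to the safety analysis.

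**What to change.** In the safety paragraph of Statistical method:

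- Keep the normal/abnormal comparison, and report high and low values separately.
- For each numeric liver and blood-count result, add the between-arm difference in Visit 4 values with a 95% confidence interval, on the log scale for liver enzymes.
- Adjust for a pre-treatment value only if one was taken. Safety assessment names these tests at Visit 4 only, so adjustment may not be possible; the randomised arms can still be compared on Visit 4 values alone.
- Present these as estimates, without significance claims.
- Leave categorical urine results as they are.

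The cost is one or two sentences and a few more table rows, with no new samples, visits or participants. The downside is that more laboratory comparisons will produce some nominal differences by chance, which is why they should be reported as estimates.
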